### Analysis

#### Sample size

The non-inferiority of birth in water compared with birth on land on rates of OASIS will be examined by parity. The Birthplace in England study found that overall 4.6% and 1.6% of nulliparous and parous women respectively, sustained OASIS.^10^ A sample size of 15 000 nulliparous and 15 000 parous low-risk women (7500 each water and land) is required to obtain 90% power, and a 95% one-sided CI around a treatment difference of zero. A non-inferiority margin of 1% or less, and 0.6% or less will be taken as clinically non-significant among nulliparous and parous low-risk women, respectively. Since nulliparous women birthing in water are regarded as the least prevalent of the four groups, the data collected would provide data on 7500 would ensure adequate numbers in the other three, more prevalent groups. These data will be combined to assess the effects averaged across both strata at an increased power, with a sample size of 30 000 low-risk women. We have assumed that 25% of the 6600 waterbirths recorded in EuroKing in 2015 were nulliparous women (1650/annum). For the infant primary outcome, an estimate of 5% is used for the proportion of infants born to low-risk mothers experiencing ‘adverse infant outcome or treatment’.^11^ A non-inferiority margin of 1.0% or less will be taken as clinically non-significant. A sample size of 16 200 infants (8100 per group water/land) are required to have 90% power, and a 95% one-sided CI around a treatment difference of zero.

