### Main analysis

Primary analysis will compare maternal and infant outcomes only between women without identified pregnancy or intrapartum complications ‘low risk’ who stay and give birth in the pool (waterbirth, group 1) compared with women without identified pregnancy or intrapartum complications ‘low risk’ who use water immersion during their labour but decide to leave the water for birth (out of water, group 2).

The primary analyses are based on a non-inferiority test of birth in water vs on land, comparing (1) the proportion of mothers that have OASIS (based on retrospective and prospective EuroKing data) and (2) the proportion of infants with a composite outcome of ‘adverse infant outcome or treatment’ (based on prospective EuroKing and NNRD data).

To test the primary hypothesis of non-inferiority between birth in water and on land, the maternal and infant primary outcomes will be evaluated for non-inferiority using logistic regression models, in the first instance with no adjustment for covariates. Adjusting for potential confounders may result in a more precise treatment effect estimate. The potential confounders of both primary outcomes (listed in table 2) will be considered. Directed acyclic graphs; visual representations of causal assumptions will be used to identify the presence of confounders.

**Table 2 T2:** Potential confounders for both maternal and infant primary outcomes

	**Maternal outcome: OASIS**	**Adverse infant composite outcome**
Maternal age (years)	X	X
Maternal BMI	X	X
Parity	X	
Duration of labour	X	X
Gestational age at delivery (weeks)	X	X
Birth weight (g)	X	X
Infant head circumference (cms)	X	
Maternal thyroid disease (including hypothyroidism)		X
Prelabour ruptured membranes		X
Intrapartum fever		X
Small for gestational age (weight <10th centile for gestational age)		X
Infant gender		X
Meconium-stained liquor		X

BMI, body mass index; OASIS, Obstetric Anal Sphincter Injury.

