The main logistic model will incorporate these selected covariates through regression adjustment. Results will be reported as an unadjusted and adjusted ORs (comparing birth in water to on land), and a two-sided 90% CI for the unadjusted and adjusted OR will be calculated. Non-inferiority will be concluded if the upper limit of the 90% CI for the difference in infant outcome between the groups is less than 1.0% (OR <1.21). Similarly, for the mother’s outcome, non-inferiority will be concluded if the upper limit of the 90% CI for the difference in the proportion of OASIS between the groups is less than 1.0% (OR <1.23) in nulliparous low-risk women and less than 0.6% (OR <1.38) in parous low-risk women. The data will then be combined to assess the effects averaged across both strata.

If non-inferiority is shown, then superiority analysis will be conducted as secondary analysis of the primary outcomes using logistic regression and will be presented as (unadjusted and adjusted) OR of outcomes in the waterbirth group compared with the birth on land group. Parameter estimates will be provided alongside 95% CI and p value. Secondary outcomes will have non-inferiority testing as detailed above.

Secondary analysis will describe the type and rates of complications among (a) low risk women who left the pool due to clinical need along with the associated maternal and infant outcomes and (b) high risk women using a pool, along with associated care (for example use of waterproof CTG cardiotocography), and maternal and infant outcomes

Maternal characteristics such as age, parity and ethnicity of all women giving birth in the study sites during data collection will be obtained and the characteristics of women who do and who not use a pool during labour, will be compared and described.

All telephone and face-to-face discussions in phase 1 and phase 2 will be audiorecorded and transcribed verbatim. For phase 1 of the qualitative component, framework analysis will be undertaken to generate key hypotheses for further exploration in phase 2. In phase 2, data will be thematically analysed initially, supported by NVivo, in order to develop an analytic framework, which will then be used to code all data.

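### The non-inferiority rule does not say whether the unadjusted or the confounder-adjusted interval decides, and the combined-parity OASIS analysis has no margin

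*Protocol article*

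**What the plan says.** All references are to the Protocol article.

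- **First test.** Main analysis evaluates both primary outcomes by logistic regression "in the first instance with no adjustment for covariates. Adjusting for potential confounders may result in a more precise treatment effect estimate". Table 2 in the same section lists the covariates as potential confounders, and directed acyclic graphs are to be used to identify confounders. The strengths and limitations list in the Abstract concedes that allocation is not random.
- **Second model and decision rule.** The section then describes the covariate-adjusted model as the main one, and says that "a two-sided 90% CI for the unadjusted and adjusted OR will be calculated". Non-inferiority is concluded from the upper limit of the 90% interval. The limits are 1.0 point (OR 1.21) for the infant composite, 1.0 point (OR 1.23) for OASIS in nulliparous women and 0.6 point (OR 1.38) in parous women. The rule does not say whether the interval meant is the unadjusted or the adjusted one.
- **Combination over parity.** "The data will then be combined to assess the effects averaged across both strata". No margin or odds-ratio limit accompanies this. The Sample size section sets margins only by stratum: "A non-inferiority margin of 1% or less, and 0.6% or less will be taken as clinically non-significant".
- **Parity figures.** The Sample size section reports that "overall 4.6% and 1.6% of nulliparous and parous women respectively, sustained OASIS", and states: "We have assumed that 25% of the 6600 waterbirths recorded in EuroKing in 2015 were nulliparous women (1650/annum". It gives no nulliparous share for women who left the pool before birth.

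**The concern.** In a randomised trial, an unadjusted primary test with adjustment added for precision is defensible. Here the women, their midwives and the course of labour determine who gives birth in water, so adjustment is needed to make the groups comparable. The precision rationale also fails on the odds-ratio scale, because covariate adjustment in logistic regression generally does not narrow the interval for the log odds ratio.

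With two intervals and one criterion, the plan allows two verdicts. If the crude interval lies below the limit and the adjusted one does not, the text supports either conclusion. In a safety question, that leaves open a finding of non-inferiority that case mix produced. The infant composite is most exposed because its test is not stratified: intrapartum fever, meconium-stained liquor and prelabour ruptured membranes are all in Table 2. The OASIS tests are protected from parity by stratification, but not from birth weight, head circumference or duration of labour.

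**Working it through.** **1. The plan's own figures reproduce.** The Sample size section asks for 90% power and "a 95% one-sided CI around a treatment difference of zero", so one-sided alpha is 0.05, which matches the two-sided 90% interval in Main analysis. With n per group = (1.645 + 1.282)² × 2p(1 − p) / margin²:

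| Outcome | p | Margin | n computed | n stated |
|---|---|---|---|---|
| OASIS, nulliparous | 4.6% | 1.0 | 7517 | 7500 |
| OASIS, parous | 1.6% | 0.6 | 7491 | 7500 |
| Infant composite | 5% | 1.0 | 8136 | 8100 |

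The odds-ratio limits, odds(p + margin)/odds(p), come to 1.230, 1.383 and 1.213, against 1.23, 1.38 and 1.21 stated. Neither the sizes nor the limits are at fault.

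**2. Which estimate decides.** Three statements in Main analysis have to be read together:

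- the test is attached first to the unadjusted model;
- the adjusted model is called the main one;
- both intervals are computed, and the criterion refers to one upper limit without naming it.

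The second statement suggests an intention. It does not cancel the first, and the third leaves the choice open.

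**3. Size within strata and for the infant composite.** The document does not say how the Table 2 variables are distributed between the groups or how strongly they act on the outcomes. Neither the size nor the direction of confounding in these tests can be calculated.

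**4. Parity in an unadjusted combined OASIS analysis.** If s is the nulliparous share of a group, its crude rate with no true effect is s × 4.6% + (1 − s) × 1.6%. The crude difference is therefore (s_water − s_land) × 3.0 points. With the plan's 25% for waterbirths, the water rate is 0.25 × 4.6 + 0.75 × 1.6 = 2.35%. The land share is not stated, so it is varied as an assumption:

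| Land share (assumed) | Land rate | Difference, water − land | OR |
|---|---|---|---|
| 20% | 2.20% | +0.15 | 1.07 |
| 25% | 2.35% | 0 | 1.00 |
| 30% | 2.50% | −0.15 | 0.94 |
| 40% | 2.80% | −0.45 | 0.84 |
| 50% | 3.10% | −0.75 | 0.75 |
| 60% | 3.40% | −1.05 | 0.68 |

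With the planned 7500 women in each of the four cells, both shares are 50% and the difference is zero.

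**5. What the document says about direction.** The Sample size section regards nulliparous waterbirths as the smallest of the four parity-by-place cells. That puts the land share above 25% only if the land group is no larger than the water group. Separately, at a 25% share, 7500 nulliparous waterbirths correspond to 7500/0.25 = 30 000 waterbirths, or 7500/1650 = 4.5 years. A water group made up of all of these would be about 25:75 by parity, not 50:50.

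**The case against.** The strongest reply is that confounding control is plainly planned. The adjusted model is called the main one, the covariates are labelled confounders, directed acyclic graphs are specified and the non-random allocation is acknowledged. On that reading the precision sentence is a slip. The criterion is also stated for a difference in proportions, with the odds ratio in brackets, and adjustment can improve precision on the difference scale. This shows what the authors intend, but it still does not say which interval decides.

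A reader might go further and infer that the plan's own rates make the combined comparison favour waterbirth. The document does not support that:

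- It gives no parity mix for the land group. The bias is zero with the planned equal cells and changes sign below a 25% land share.
- The quoted wording on averaging can be read as a stratified combination, and parity is a listed OASIS confounder. Nowhere does the document say that the strata are collapsed without it.
- Each stratum is tested against its own margin first, so a combined result cannot overturn a stratum's failure.

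Nor can one calculate how often a combined analysis would wrongly declare non-inferiority, because the plan sets no combined margin and announces no combined verdict.

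Finally, a combined margin or a standardisation method may be left to an analysis plan that is not shown. That limits the point on the combined analysis. It does not excuse a decision rule that the article does state and leaves ambiguous.

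**Conclusion.** The point holds in a limited form. The primary test is attached first to an unadjusted model in a non-randomised cohort, adjustment is justified by precision although its purpose is to remove confounding, and the single criterion does not name the deciding interval. This affects both OASIS stratum tests and the infant composite; the size there cannot be derived from the document.

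For the combined OASIS analysis, the missing margin is a fact of the text. The parity bias is conditional: it arises only in an unadjusted combination and only if the parity mix differs between groups. The range of −0.45 to −1.05 points illustrates an assumed land share of 40% to 60% and is not a prediction. The change is worth making because it costs almost nothing and removes a route to an unsupported safety conclusion.

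**What to change.** 1. State that non-inferiority is concluded only from the confounder-adjusted estimate and its 90% interval, and that unadjusted estimates are descriptive.
2. Replace the precision sentence with one that gives control of confounding as the reason for adjustment.
3. For OASIS, leave the non-inferiority decisions to the nulliparous and parous strata. Keep parity in the combined model, or stratify by it, and report the combined result as an estimate with an interval and no non-inferiority verdict.

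This is a change of wording only. It needs no new data and no change to the sample size. If the analysis plan already names the deciding estimate, the protocol text should be brought into line with it.

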**Ethics and dissemination:**

The protocol has been approved by NHS Wales Research Ethics Committee (18/WA/0291) the transfer of identifiable data has been approved by Health Research Authority Confidentiality Advisory Group (18CAG0153).

Study findings and innovative methodology will be disseminated through peer-reviewed journals, conferences and events. Results will be of interest to the general public, clinical and policy stakeholders in the UK and will be disseminated accordingly.

Strengths and limitations of this studyUsing large retrospective and prospective datasets concomitantly provides six years data over a three year study period.Ability to look at all neonatal outcomes and treatments across the wide geographical range and number of units.Using existing, routine data enhanced by prospective data to investigate the safety of waterbirth across a range of outcomes.Data collected will only represent users of Wellbeing Software’s EuroKing maternity software system.Allocation is not random, so unmeasured confounding is possible.

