### Data providers and datasets

To answer the research questions, two datasets will be used, data extracted from EuroKing maternity software system and data held by the NNRD. EuroKing forms a comprehensive clinical dataset and is currently used by 26 of the maternity NHS Trusts and Health Boards in the UK. All 200 NNUs in England, Wales and Scotland form the UK Neonatal Collaborative and contribute electronic health record data to the NNRD. The NNRD is a national resource formed of the Neonatal Dataset (an NHS Information Standard), comprising of 450 clearly defined variables extracted at patient level from the commercial electronic health record used by all UK NNUs. For the purpose of the POOL study, NNRD data will only be used from England and Wales, as no units in Scotland are supported by WS.

For the retrospective data collection, the data extract will be created by WS for the period January 2015 until prospective data collection commences (site opening). This extract will be created remotely by WS accessing the participating site’s server. A unique study number will be generated prior to data leaving the study sites. WS will transfer a pseudonymised version of this extract to CU and a separate extract of data containing the unique study number, and identifiers to NNRD (pool use) using a secure file transfer process. NNRD will proceed to match the data received from WS to ensure complete records are obtained for infants transferred to NNU and send the pseudonymised dataset to CU.

For prospective data, the same format will be followed as for the retrospective data. Prospective data extracts will include the new variables added to EuroKing (overview of key data items in table 1). A separate syntax will direct the NHS number, unique study number and other identifiers of infants born to all women who used a pool during labour, after site opening, to the NNRD.

**Table 1 T1:** Data sources

**Data provider**	**Data source**	**Data collection period**	**Key data items**
Wellbeing Software	NHS site (Maternity unit)	From January 2015	Routinely collected data items: Demographics (including parity, age, ethnicity and deprivation) Use of pool for labour analgesia/waterbirth Maternal health Labour Birth Pregnancy history Maternal medical and obstetric history Midwifery or obstetric led intrapartum care Delayed cord clamping (>60s after birth) Type of intended care throughout labour Maternal health conditions

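### Table 2, the printed list of potential confounders, omits ethnicity and deprivation without a reason, although both are routinely collected from January 2015

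*Protocol article*

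**What the plan says.** Four places in the protocol article bear on this point.

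- **Data available.** Table 1 (Data providers and datasets) lists "Demographics (including parity, age, ethnicity and deprivation" among the routine EuroKing items, with a collection period from January 2015. For the retrospective part, "the data extract will be created by WS for the period January 2015 until prospective data collection commences (site opening". Prospective extracts keep the same format and add the new variables.
- **Candidate confounders.** Main analysis says "The potential confounders of both primary outcomes (listed in table 2) will be considered". Table 2 then gives one column per primary outcome. Neither ethnicity nor deprivation appears in either column.
- **Selection and model.** "Directed acyclic graphs; visual representations of causal assumptions will be used to identify the presence of confounders". After Table 2 the text continues: "The main logistic model will incorporate these selected covariates through regression adjustment".
- **Where ethnicity does appear in the analysis.** "Maternal characteristics such as age, parity and ethnicity of all women giving birth in the study sites during data collection will be obtained". This belongs to the descriptive comparison of women who do and do not use a pool. Deprivation is not mentioned in the analysis text.

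The strengths and limitations concede that "Allocation is not random, so unmeasured confounding is possible". They say nothing of confounders that are measured but not on the list.

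**The concern.** Group 2 is defined as low-risk women who left the water with no clinical or risk-based reason, so exposure is largely a matter of personal choice. Such a choice may be socially patterned. If the same social factors also relate to OASIS or to the infant composite, leaving them out of the model biases the primary estimates.

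The conclusion at stake is a safety claim by non-inferiority. Bias that flatters waterbirth would make a false claim of non-inferiority more likely. Bias the other way would make a true one harder to show. Table 2 is specific enough to name maternal thyroid disease and infant head circumference, so the absence of two standard demographics already in the extract stands out.

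**Working it through.** **1. Table 1 against Table 2.** Table 1 names four demographics as routinely collected.

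| Table 1 demographic | Table 2, OASIS | Table 2, infant composite |
|---|---|---|
| Age | listed | listed |
| Parity | listed | not listed |
| Ethnicity | not listed | not listed |
| Deprivation | not listed | not listed |

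Table 2 has 7 candidates for OASIS and 11 for the infant composite. The omission is confirmed for both outcomes.

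**2. Can they be mediators?** Both characteristics precede labour and therefore precede the decision to stay in or leave the pool. They cannot lie on a path from waterbirth to the outcome, so adjusting for them cannot remove part of the effect in that way.

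**3. Are they shown to be confounders?** No. That requires an association with staying or leaving among pool users and with the outcome. The protocol reports neither.

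**4. The plan's own figures.** With n per group = 2p(1 − p)(1.645 + 1.282)²/margin², 90% power, one-sided 5% and a true difference of zero:

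- nulliparous OASIS (4.6%, margin 1.0 point): 7517, stated 7500;
- parous OASIS (1.6%, margin 0.6 points): 7491, stated 7500;
- infant composite (5%, margin 1.0 point): 8136, stated 8100.

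The margin odds ratios, odds(p + margin)/odds(p), are 1.230, 1.383 and 1.213, against the stated 1.23, 1.38 and 1.21. All reproduce, and none changes if two candidates are added.

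**5. Scale illustration, on assumed inputs.** Take one unadjusted binary factor with risk ratio RR and prevalence pw in the water group and pl in the land group. The prevalences and RR are assumptions and are not in the document.

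Confounding ratio R = [1 + pw(RR − 1)]/[1 + pl(RR − 1)]. Shift in the risk difference = risk × (R − 1).

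*Factor rarer in the water group* (10% v 15%, RR 2): R = 1.10/1.15 = 0.957.

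- Nulliparous OASIS: the shift is 4.6 × 0.0435 = 0.20 to 5.6 × 0.0435 = 0.24 points towards waterbirth.
- With the true difference at the margin, SE = √[(0.046 × 0.954 + 0.056 × 0.944)/7500] = 0.359 points.
- The chance of wrongly concluding non-inferiority is Φ(0.243/0.359 − 1.645) = Φ(−0.967), about 17% instead of 5%.
- Infant composite: 0.22 to 0.26 points, about 18%.
- With RR 1.5, R = 1.05/1.075 = 0.977. The nulliparous shift is 0.11 to 0.13 points and the infant shift 0.12 to 0.14 points, with an error rate of about 10% for each.

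*Factor commoner in the water group* (15% v 10%, RR 2): R = 1.15/1.10 = 1.045.

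- Nulliparous OASIS: the shift is 4.6 × 0.0455 = 0.21 points against waterbirth.
- With a true difference of zero, SE = √(2 × 0.046 × 0.954/7500) = 0.342 points.
- Power is Φ((1.0 − 0.209)/0.342 − 1.645), about 75% instead of 90%. The false non-inferiority rate falls below 5%.

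Stronger imbalances give larger shifts. With 10% v 25% and an outcome odds ratio of 2.5, the nulliparous shift is 0.71 points. Nothing in the document says which case applies, if any.

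**The case against.** The strongest reply is that Table 2 is nowhere called exhaustive. Its entries are only to be considered, and causal graphs then identify the confounders. The covariates in the main model may be whatever set remains after that step, and the analysis plan, which is not shown, could add variables. This stands to an extent: a reader might infer that the protocol bars ethnicity and deprivation from the model, and the text does not say so. It does not say either that the graphs may reach beyond the table. The article also chose to print an outcome-specific list rather than defer it.

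Three other stronger readings also go too far.

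- The protocol's comparison by ethnicity might be taken as evidence of confounding. It contrasts pool users with non-users, whereas the primary comparison is among pool users only.
- Table 1 might be read as saying both items are recorded for every birth. It says they are routinely collected and gives no completeness.
- The 17% and 18% figures might be quoted as the study's error rate. They rest on invented prevalences and risk ratios, and the reversed imbalance lowers that rate. They also treat the factor as wholly unadjusted. Age, BMI, gestational age and birth weight are already candidates and may carry part of any social effect.

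These limits do not explain why two measured, pre-labour characteristics are left off the list.

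**Conclusion.** The point holds as an unexplained omission from a printed list. Two plausible baseline confounders of a choice-based exposure, both routinely collected from January 2015, are missing from Table 2 for both primary outcomes. The documents do not show that either variable does confound, and the size and direction of any bias cannot be derived from them. It could favour or disfavour waterbirth. Under modest assumed imbalances the shift is about 0.1 to 0.3 points for nulliparous OASIS and for the infant composite, against margins of 1.0 point. That is enough to justify listing the variables, but it is not an estimate of actual bias. The sample size and margins are unaffected.

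**What to change.** Add maternal ethnicity and area deprivation to Table 2 as candidates for both primary outcomes, and enter both in the directed acyclic graphs. Adjust for them in the main logistic models unless the graph justifies leaving them out, and in that case state the reason.

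The cost is two rows in a table and a few degrees of freedom, which is minor with 15 000 women planned per parity stratum and 16 200 infants. Because completeness is not stated, some provision for missing values will be needed. No new data collection and no change in sample size follow.

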This study is collecting data on births to all women in 26 UK maternity units from 2015 and is identifying the numbers, proportion and characteristics of women who use water immersion during labour or birth. The study will also establish whether waterbirth is as safe for mothers and their infants as using a pool during labour but getting out prior to birth. Data will be collected on 15 000 waterbirths and 15 000 land births among women with uncomplicated pregnancies from National Health Service (NHS) sites which use Wellbeing Software’s (WS) maternity software system EuroKing. This study will use data recorded routinely as part of standard maternity care and stored on respective NHS site’s servers. For infants admitted to a neonatal unit (NNU), the study will also use data held by the National Neonatal Research Database (NNRD). Data needed to answer some study questions are already recorded, for example, perineal trauma, therefore, data from births from 2015 onwards can be included. Existing, routinely collected data does not capture all information to answer the study questions, data items missing from existing routinely collected data include infants receiving antibiotics without admission to NNU and whether following waterbirth the placenta is delivered in or out of water. Cardiff University (CU) has worked with WS in order to develop study specific data fields which will enable these data to be captured in participating sites from 2019 onwards.

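### Table 2 lists parity as a candidate confounder for OASIS but not for the infant composite, so a plausible parity imbalance could remain in the infant comparison

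*Protocol article*

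**What the plan says.** The Main analysis section of the Protocol article presents the candidates for adjustment in Table 2, under the title "Potential confounders for both maternal and infant primary outcomes". Parity has a mark in the OASIS column and none in the infant column. The infant column is otherwise broad, with 11 entries: maternal age, BMI, duration of labour, gestational age, birth weight, thyroid disease, prelabour ruptured membranes, intrapartum fever, small for gestational age, infant gender and meconium.

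On how the list is used, the same section says: "The potential confounders of both primary outcomes (listed in table 2) will be considered". Selection is by directed acyclic graph: "visual representations of causal assumptions will be used to identify the presence of confounders". Then: "The main logistic model will incorporate these selected covariates through regression adjustment".

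OASIS is tested separately in nulliparous and parous women, each with its own margin, and then pooled. Nothing similar is stated for the infant outcome, which has one rate (5%), one margin (1.0 percentage point) and one target (8100 per group).

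On how parity relates to place of birth, the Sample size section says "We have assumed that 25% of the 6600 waterbirths recorded in EuroKing in 2015 were nulliparous women (1650/annum" and "Since nulliparous women birthing in water are regarded as the least prevalent of the four groups".

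**The concern.** A confounder has to be related to both exposure and outcome. Both primary outcomes compare the same two groups: women who give birth in the pool and women who leave it. By listing parity for OASIS, the plan already treats it as possibly related to that exposure, and the sample size assumptions point the same way. Leaving parity off the infant list is then safe only if it has no relation to the infant composite beyond what the listed covariates carry. The article does not argue this.

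The candidates to be considered are the ones in Table 2. As written, parity therefore enters the infant analysis neither as a covariate nor as a stratum. If first births carry more respiratory support or antibiotic use, and are less common in the water group, the water group looks better for a reason unrelated to water. In a non-inferiority test of safety, that error favours the conclusion that waterbirth is safe.

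**Working it through.** **1. Reproduce the plan's own figure.** Inputs from Sample size: 5% in both groups, margin 0.01, one-sided alpha 0.05, power 90%.

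n per group = (1.645 + 1.282)² × 2 × 0.05 × 0.95 / 0.01² ≈ 8136, against 8100 stated. Power at 8100 is 89.9%. The odds-ratio margin also reproduces: (0.06/0.94)/(0.05/0.95) = 1.213, stated as 1.21. No stated figure is wrong.

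**2. What the plan implies about parity on land.** The nulliparous share in water is 1650/6600 = 25%. The Introduction plans equal totals: "Data will be collected on 15 000 waterbirths and 15 000 land births among women with uncomplicated pregnancies". The infant target is also equal, at 8100 per group. Take 100 births per group, so that water has 25 nulliparous and 75 parous. For nulliparous water to be the smallest cell, land must have more than 25 nulliparous and more than 25 parous. The land share s is then above 25% and below 75%.

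This depends on equal totals. Land cells of 30 nulliparous and 120 parous still leave 25 as the smallest cell, but the land share is 20%, so the imbalance reverses.

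**3. Crude bias with no effect of water within parity.** Assumed, because the documents give neither: the land share s, and the risk ratio RR for the infant composite (nulliparous against parous). The land rate is fixed at the plan's 5%.

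- Parous rate p = 0.05 / (1 − s + s × RR); nulliparous rate = RR × p
- Water minus land = (0.25 − s) × (RR − 1) × p

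With s = 40% and RR = 1.5: p = 0.05/1.20 = 4.17%, nulliparous 6.25%, difference = −0.15 × 2.08 = −0.31 points.

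With s = 50% and RR = 1.5: p = 0.05/1.25 = 4.00%, nulliparous 6.00%, difference = −0.25 × 2.00 = −0.50 points.

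**4. False non-inferiority at a true 1.0-point harm within each parity group.** With d the bias from step 3, the probability is Φ(−d/SE − 1.645), at 8100 per group.

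- s = 40%: water rate 5.69%, SE = √[(0.0569 × 0.9431 + 0.05 × 0.95)/8100] = 0.00353; Φ(0.884 − 1.645) = 22.3%
- s = 50%: water rate 5.50%, SE = 0.00350; Φ(1.427 − 1.645) = 41.4%

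**5. Range.** Each cell gives the crude bias in points, with the false non-inferiority rate in brackets (nominal 5%).

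| Land share nulliparous | RR 0.8 | RR 1.0 | RR 1.25 | RR 1.5 | RR 2.0 |
|---|---|---|---|---|---|
| 25% | 0 (5.0%) | 0 (5.0%) | 0 (5.0%) | 0 (5.0%) | 0 (5.0%) |
| 35% | +0.11 (2.6%) | 0 (5.0%) | −0.12 (9.3%) | −0.21 (14.8%) | −0.37 (27.6%) |
| 40% | +0.16 (1.8%) | 0 (5.0%) | −0.17 (12.2%) | −0.31 (22.3%) | −0.54 (45.5%) |
| 50% | +0.28 (0.8%) | 0 (5.0%) | −0.28 (19.5%) | −0.50 (41.4%) | −0.83 (77.9%) |
| 60% | +0.40 (0.3%) | 0 (5.0%) | −0.38 (28.6%) | −0.67 (61.4%) | −1.09 (94.1%) |

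All of these describe the comparison before any covariate adjustment.

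**The case against.** A reader might infer that the plan's figures show waterbirth to be strongly patterned by parity, and hence that the infant result is confounded in favour of water. The documents do not support that, for four reasons.

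- The 25% is itself an assumption. It covers all waterbirths recorded in 2015, and no parity share is given for women who leave the pool. The bounds in step 2 allow anything from almost no imbalance to a large one.
- The link from parity to the infant outcome is not documented. The 4.6% and 1.6% rates by parity are for OASIS. The infant rate is a single 5%.
- The main model is adjusted. Duration of labour, birth weight, maternal age, fever and meconium are likely routes by which first births would differ, so part of any parity effect would be removed. The crude figures do not estimate the bias that remains.
- Table 2 is a list of potential confounders with graph-based selection, not a final adjustment set.

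The first three limit what can be said about direction and size, and they stand. The fourth helps less than it seems to. The candidates are those in the table, and parity is not among them for the infant outcome, so the article gives no sign that it will be considered. The listed covariates may stand in for parity, but nothing ensures that they do so fully. The unadjusted infant odds ratio, also to be reported with its 90% CI, gets no such protection.

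**Conclusion.** The omission is clear and sits awkwardly with the plan's own treatment of parity for the same exposure comparison. It should be fixed. Bias towards non-inferiority in the infant result is plausible but not demonstrated. It requires a higher nulliparous share on land, which the plan's assumptions suggest, and a higher infant composite risk in first births, which the documents do not address.

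Under moderate assumptions (land share 40 to 50%, risk ratio 1.5, land rate 5%), the crude bias is about a third to a half of the 1.0-point margin. It vanishes if the risk ratio is 1 or the shares are equal, and it reverses if the risk ratio is below 1. Harsher inputs give larger figures. For example, 50% nulliparous on land with rates of 7% and 4% gives −0.75 points and a false non-inferiority rate of about 67%. Those rates are chosen, not sourced; they put the land rate at 5.5%, and they too describe the crude comparison only. They should not be read as the expected error of the planned adjusted analysis.

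Confidence is high in the omission and moderate in the direction and size of the bias.

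**What to change.** In Table 2, mark parity (nulliparous/parous) for the adverse infant composite, and include it in the adjusted infant model. This removes the bias due to parity mix and leaves the target of 8100 per group unchanged. If the causal graph gives a reason to leave parity out, that reason should be stated.

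Showing the infant result by parity is optional and should be labelled descriptive, because the infant sample is sized for the overall comparison.

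The cost is a change of wording. Table 1 already lists parity among the items collected routinely from January 2015, so no new data are needed.
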